### Cost Outcomes

Two cost outcomes will be used

(i) *Participants resource utilization *will be assessed using cost diaries developed and successfully used by the Principal Investigator in a previous RCT [54]. A random sample of 20% of cost diaries in each group will be verified by telephone interview with a researcher not involved in the day to day running of the trial to check the accuracy and ensure the quality of the data.

(ii) *Participant's health state *will be assessed using the EuroQol (EQ-5D) Questionnaire's Weighted Health Index [45] and Visual Analogue Scale.

Follow-up reminders will be given by phone and completed questionnaires returned by pre-paid envelopes.

### Interventions

#### (i) Supervised exercise class (SEC)

Within one week of randomisation, participants will commence the SEC. This class will follow a group-based format based on the 'Back to Fitness' programme used in the UK BEAM trial [9-11,13,14] which is underpinned by cognitive behavioural therapy principles designed to change participants behaviour by modifying their attitude to their LBP, i.e. 'hurt' does not mean harm [7,8]. First, each participant will attend the physiotherapy department for an initial individual assessment with the Chartered Physiotherapist delivering the class, where there will be discussion and agreement between the therapist and the patient on short and long-term goals; recording of the patient's exercise capabilities and perceived barriers to recovery and the individual's treatment expectations. Second, participants will attend the physiotherapy department of the relevant participating hospital once a week for 8 weeks for a one-hour supervised group exercise class led by a Chartered Physiotherapist. The physiotherapist will advise patients according to their individual goals and exercise capabilities, and help identify which exercise(s) they could continue independently of the treatment sessions, i.e. foster the development of self-management strategies. Subjects will also be required to rate their perceived exertion during the class on the Borg scale – a linear scale measuring level of breathlessness from 0= 'not breathless at all' to 10 = 'maximal'. [55,56]. Patients will be encouraged to accept responsibility for determining and carrying out their weekly programme of activity. Adherence with the supervised exercise programme will be recorded as the number of sessions attended. The number of sessions defined as adherence will be decided on completion of the trial.

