### Sample Size

A total of 189 patients (n = 63 per group) will be required for 80% power to detect a 4 point difference between groups on the primary outcome, the Oswestry Disability Index [39], with 95% confidence using a two-tail between-within repeated measures ANOVA test of difference between group means. Based on the results of previous LBP trials investigating exercise [11] and using postal follow-ups [40], we anticipate a 30% loss to follow-up. Thus we aim to recruit 82 subjects per group (total 246 subjects).

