### Data Analysis

Analysis will be by intention to treat. All participants and group allocation will be coded, sociodemographic data coded, and outcome questionnaires scored, and all data entered into the Statistical Package for the Social Sciences database for analysis following data cleaning and checking for errors. Analysis of the clinical outcome data will be performed by the statistician who will remain blinded to group identification until analysis is complete. Between group analyses will be performed to test for between group differences in each outcome from baseline at follow-up. Continuous outcome variables will be analysed using a mixed between-within repeated measures analysis of variance if the assumptions for parametric statistics hold. If substantial evidence of non-normality is found appropriate alternative (non-parametric) tests will be applied, and specified as the primary analysis method.

Using data from the cost diaries, the extent to which each of the interventions has impacted on subsequent use of health care will also be calculated and will cover all identifiable health care costs. The direct and indirect costs to patients receiving each intervention will be obtained. The health care services costs incurred during the intervention and year to follow up will be calculated using the relevant observable prices. Where prices cannot be observed shadow prices will estimated; mean and median health care utilization rates and associated direct service costs in addition to indirect and direct patient costs will be calculated for both intervention groups. Relationships between presenting LBP severity and utilization/cost will be investigated. An additional cost effectiveness analysis will use the magnitude of a mean and median change on the Oswestry Disability Questionnaire as the natural unit of outcome.

The resulting scores from the EQ-5D health state and the visual analog scale will be used to generate the health state utility values necessary for the within trial cost utility analysis (CUA). The CUA will allow the outcomes of this study to be compared to other studies allowing the relevant short term benefit of the interventions to be assessed.

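### Group delivery of the supervised class arm is not allowed for in the stated ANOVA or the 80% power, so any positive class-level correlation makes SEC contrasts look too precise

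*Protocol article*

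**What the plan says.** Under Interventions, SEC patients attend the department "once a week for 8 weeks for a one-hour supervised group exercise class led by a Chartered Physiotherapist". The physiotherapist who runs the class also carries out the initial individual assessment. WP patients have an individual assessment and weekly telephone calls from the physiotherapist who assessed them. UP patients are treated one to one.

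Patients are randomised individually, with hospital as the only stratification factor (Randomisation).

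The Data Analysis section states: "Continuous outcome variables will be analysed using a mixed between-within repeated measures analysis of variance", subject to parametric assumptions. It mentions no class, therapist or hospital term.

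The Sample Size section uses the same test: "A total of 189 patients (n = 63 per group) will be required for 80% power to detect a 4 point difference between groups" on the ODI, "with 95% confidence using a two-tail between-within repeated measures ANOVA test of difference between group means". It gives no SD, ICC, class size or design effect.

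**The concern.** Only one of the three arms is delivered to groups, so the design is partially nested. People who share a class share its leader, its dynamics and its timing, and their outcomes may be correlated as a result. In the named ANOVA, the between factor is treatment group and the within factor is time. It handles repeated measurements on one patient but takes different patients as independent.

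If the class-level ICC is positive, the variance of the SEC mean is larger than this model reports. SEC enters two of the three pairwise contrasts behind the primary objective, the difference between groups in ODI change at 6 months. Both contrasts would then have intervals that are too narrow, a type I error above 5% and less power than stated.

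**Working it through.** **Inputs from the protocol article.** Difference 4 ODI points, two-sided 5%, 80% power and 63 analysed per group (Sample Size). Five hospitals (Methods/design).

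**Assumptions, none of them in the article.** SD 8; m = 4 to 10 analysed SEC patients per class; ICC 0.01 to 0.05; clustering in SEC only; normal approximation; each contrast treated as a comparison of two means.

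**Step 1: the plan's own figure.** For independent patients, n = 2 × [SD × (1.96 + 0.84) / 4]². Setting n = 63 and solving gives SD = 8.01. With SD 8, n = 62.8, rounded up to 63, or 189 in total. Power at 63 is Φ(4 / (8 × √(2/63)) − 1.96) = Φ(4/1.425 − 1.96) = 80.1%. The stated size therefore agrees with an independent-patient calculation without a design effect. This is consistency, not proof, because the SD was free to choose.

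**Step 2: add class clustering in SEC.**
- Design effect in SEC: DE = 1 + (m − 1) × ICC
- True SE of an SEC contrast: 8 × √((DE + 1)/63)
- SE ratio, true to nominal: √((DE + 1)/2)
- Type I error of the unadjusted test: 2 × [1 − Φ(1.96 / SE ratio)]
- Power with the correct SE: Φ(4/SE − 1.96)

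Example with m = 8 and ICC 0.05: DE = 1 + 7 × 0.05 = 1.35. SE = 8 × √(2.35/63) = 1.545 against a nominal 1.425, a ratio of 1.084. Type I error = 2 × [1 − Φ(1.808)] = 7.1%. Power = Φ(4/1.545 − 1.96) = 73.5%.

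| m | ICC | DE | SE ratio | Type I error | Power at 63 |
|---|---|---|---|---|---|
| 4 | 0.01 | 1.03 | 1.007 | 5.2% | 79.5% |
| 4 | 0.02 | 1.06 | 1.015 | 5.3% | 79.0% |
| 4 | 0.05 | 1.15 | 1.037 | 5.9% | 77.2% |
| 8 | 0.01 | 1.07 | 1.017 | 5.4% | 78.8% |
| 8 | 0.02 | 1.14 | 1.034 | 5.8% | 77.4% |
| 8 | 0.05 | 1.35 | 1.084 | 7.1% | 73.5% |
| 10 | 0.01 | 1.09 | 1.022 | 5.5% | 78.4% |
| 10 | 0.02 | 1.18 | 1.044 | 6.0% | 76.7% |
| 10 | 0.05 | 1.45 | 1.107 | 7.7% | 71.8% |

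**Step 3: small-sample degrees of freedom.** The normal approximation flatters a valid test when clusters are few. Take the extreme of one SEC cluster per hospital: k = 5 and m = 63/5 = 12.6. With v₁ = 64 × DE/63 and v₂ = 64/63, Satterthwaite gives df = (v₁ + v₂)² / [v₁²/(k − 1) + v₂²/62]. At ICC 0.01 df is about 14 and power 72%, against 78% by the normal formula. At ICC 0.05 df is about 10 and power 61%, against 70%.

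**Step 4: therapists.** WP and UP patients also have a treating physiotherapist, so therapist clustering is not confined to SEC. Again take five clusters per arm (m = 12.6). If each arm has its own therapists, the ratio in both arms is √DE, and the unadjusted test has type I error 7.7% at ICC 0.02 and 11.9% at ICC 0.05. If the same five therapists serve both arms, their effects cancel in the contrast: simulation of an unadjusted t-test gave about 4.8% and 4.5%. The article does not say which applies.

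**The case against.** **The article is condensed, and random effects are commonly left to an analysis plan.** This is fair as far as silence goes: the sentence on the ANOVA does not even list hospital. But the article names both the test and the power basis, and neither accommodates the group delivery that it describes. The point rests on that mismatch, not on a missing detail.

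**A reader might infer that the SEC error bars are shown to be wrong.** The documents do not support that. They give no ICC, class size, number of classes or number of therapists, and at ICC 0.01 the effect is trivial. Training, a trial manual, a 20% record audit and individual goals within classes may hold the ICC down. The primary time point is 6 months, well after the 8-week classes end. These measures make a small ICC more plausible, but they do not correct a standard error.

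**A reader might also take the worst case as the expected one.** Type I error of 9.5% and power of 67% need 16 analysed patients per cluster at ICC 0.05. That exceeds the average of 12.6 obtained even with one cluster per hospital for the whole trial. Patients start within a week of randomisation, which suggests rolling entry and smaller, overlapping groups. That is an inference, and it also makes the simple design effect approximate.

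**A therapist effect cannot be charged to SEC alone.** This stands. Therapist clustering may exist in every arm, and its direction depends on whether therapists are shared across arms. Randomisation is stratified by hospital, so leaving hospital out of the model tends to make standard errors too large, which works the other way.

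**Conclusion.** The concern holds conditionally. The SEC arm is delivered in classes, and the stated ANOVA and the 80% power allow only for within-patient correlation. If class-mates' outcomes are positively correlated, SEC versus UP and SEC versus WP will be reported too precisely, with power below 80%. WP versus UP is unaffected by class clustering.

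Under the assumptions listed (SD 8, 4 to 10 analysed per class, SEC only, normal approximation), the effect is negligible at ICC 0.01 and material at about ICC 0.05, where type I error is 5.9-7.7% and power 72-77%. A valid test with few clusters would have lower power still. Nothing here shows the trial to be invalid. The plan leaves an avoidable uncertainty in two of its three contrasts.

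**What to change.** 1. Record class and therapist identity for every participant on the treatment record form that clinicians already complete. This must be done prospectively, since it may be hard to reconstruct later.
2. Include hospital, the stratification factor, in the ODI analysis.
3. Prespecify, as a sensitivity analysis reported beside the primary result, a partially nested linear mixed model with a random class effect in SEC, a therapist effect where therapists are identified, and small-sample degrees of freedom.
4. State in the Sample Size section that 80% power assumes no clustering, and give the power for ICC 0.01 to 0.05 at the expected class size.

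The cost is two identifiers on an existing form, some analysis wording and a less favourable power statement. Treatment and recruitment do not change. The downside is wider SEC intervals in the sensitivity analysis and a variance component that is poorly estimated with few classes. With as few as five clusters the loss of power is considerable, so making this model primary would be debatable; hence its place as a sensitivity analysis.

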(iii) determine the difference between groups in cost utility and the cost effectiveness of the alternative treatment programmes

(iv) determine the difference between groups in level of adherence to each intervention

(v) complete a qualitative exploration of subjects experience of each intervention

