#### Assessors

A blinded researcher will administer all outcome measures for postal follow-up. The Trial Co-ordinator will not be involved in follow-up outcome assessment. The statistician will be unaware of group allocation until completion of data analyses.

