Participants will be contacted once per week by telephone by the Chartered Physiotherapist who performed the initial assessment to progress their walking frequency and duration based on their exercise diary record of the previous week's walking, and to provide encouragement. These telephone calls will be based around a specifically developed telephone script based upon CBT principles. Participants will be advised that just like athletes, any unaccustomed exercise is likely to produce some muscle soreness [8]. Participants will use their Yamax Digiwalker Pedometer [60] as a motivational feedback tool, providing immediate information on activity levels [61].

Adherence with the walking programme will be assessed by the frequency, distance, number of steps taken and duration of walks recorded in the exercise diary. Specific adherence levels will be established once the trial is complete. At the end of the intervention subjects will reattend the physiotherapy department for a review appointment with a view to discharge from physiotherapy.

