#### (iii) Usual Physiotherapy (UP) -Control Group

Within one week of randomization, participants will commence individual usual physiotherapy at the discretion of the treating physiotherapist in the participating hospital. All physiotherapy treatments and the number of visits will be recorded for the study period in previously designed treatment record forms. On the basis of a previous RCT by the Principal Investigator in the Republic of Ireland public physiotherapy health service the anticipated mean (SD) number of treatments is 5.8 over a mean (SD) of 7.7 weeks (5.8) weeks [54]. A multimodal approach of education/advice, manipulative therapy and exercise therapy will be permitted on the basis of the results of previous surveys of physiotherapy practice in the UK and Ireland [32-34]. As part of this it is expected that subjects will be provided with an individualized exercise programme at the discretion of the treating therapist but will not be permitted to attend group exercise class or undertake a walking programme during the trial. Adherence will be assessed by the number of visits prior to discharge from physiotherapy.

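### Adherence thresholds for the class and walking arms are to be set after the trial ends, and the three arms measure adherence on different scales, so secondary objective (iv) is open to data-driven definition

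*Protocol article*

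**What the plan says.** The objectives at the end of the Background section of the protocol article include, as secondary objective (iv), to "determine the difference between groups in level of adherence to each intervention". The Interventions section then defines adherence arm by arm.

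- **Supervised exercise class.** Classes run "once a week for 8 weeks for a one-hour supervised group exercise class". The measure is named: "Adherence with the supervised exercise programme will be recorded as the number of sessions attended". The threshold is postponed: "The number of sessions defined as adherence will be decided on completion of the trial".
- **Walking programme.** "Adherence with the walking programme will be assessed by the frequency, distance, number of steps taken and duration of walks recorded in the exercise diary". No rule combines the four quantities. The threshold is again postponed: "Specific adherence levels will be established once the trial is complete".
- **Usual physiotherapy.** "Adherence will be assessed by the number of visits prior to discharge from physiotherapy". No threshold is mentioned, now or later, and no number of visits is prescribed. The 5.8 treatments quoted in that section are an expected mean from a previous trial.

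Under Blinding, Assessors: "The statistician will be unaware of group allocation until completion of data analyses". The Data Analysis section repeats that blinding and states that analysis is by intention to treat.

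**The concern.** A comparison between groups that is announced as an objective should rest on a definition settled before the data can influence it. Here the article commits to the opposite for two of the three arms. A separate analysis plan would not normally cure this, because a plan that fixed the thresholds beforehand would contradict what the article states.

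The comparison is also weak for a second reason. Classes attended out of 8, a set of walking-diary quantities and an open-ended visit count are not the same kind of quantity. In usual physiotherapy a low count cannot separate a patient discharged early from one who stopped attending, because appointments offered are not part of the measure.

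What is at stake is the credibility of any statement that one programme was better adhered to than another. Readers will look for such a statement, since the Background gives poor adherence and drop-out from classes as part of the case for a walking programme.

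**Working it through.** The plan gives no figure to reproduce, so the first check is of the text.

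| Arm | Named measure | Denominator | Threshold |
|---|---|---|---|
| Exercise class | sessions attended | 8 weekly classes | after the trial |
| Walking | frequency, distance, steps, duration | none stated | after the trial |
| Usual physiotherapy | visits before discharge | none stated | none |

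No two rows share a scale. The explicit postponement applies to the first two rows only.

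**Does blinding protect the choice?** The Assessors and Data Analysis statements keep the statistician unaware of allocation. They do not say who sets the thresholds or what that person will have seen. The measures also differ by arm: class attendance, a walking diary and a visit count each reveal the group.

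**Hypothetical size of the problem.** The documents give no attendance distribution, so the following is an assumption. It uses two arms with identical attendance on a 0 to 8 scale, which no pair of arms in this trial actually has. The group sizes, 82 recruited and 63 required per group, come from the Sample Size section.

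*Model A: attendance varies between people.* Attendance is Binomial(8, π) with π from Beta(2, 1). This gives P(X = k) = (k + 1)/45 for k = 0 to 8. The share classed as adherent is then:
- at least 4 sessions: (5 + 6 + 7 + 8 + 9)/45 = 35/45 = 78%
- at least 5: 30/45 = 67%
- at least 6: 24/45 = 53%
- at least 7: 17/45 = 38%
- all 8: 9/45 = 20%

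*Model B: constant attendance probability 0.7 per session, Binomial(8, 0.7).* The shares are 94%, 81%, 55%, 26% and 6% for cut-offs 4 to 8. At 0.6 they run from 83% down to 2%, and at 0.8 from 99% down to 17%.

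For each simulated trial and each cut-off c, with p the share at or above c, the test is z = (p1 − p2)/√(2p̄(1 − p̄)/n), called significant when |z| > 1.96. The false-positive rate is the share of trials with at least one significant result among the cut-offs allowed, using the same cut-off in both arms.

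| Cut-offs allowed | Model A, n = 82 | Model B, n = 63 |
|---|---|---|
| one, fixed in advance | about 5% | about 5 to 6% |
| best of 5 to 7 | about 11% | about 13 to 14% |
| best of 4 to 7 | about 14% | – |
| best of 4 to 8 | – | about 19% |
| best of 1 to 8 | about 24% | – |

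A dash marks a combination not reported here. The 24% includes cut-offs such as at least 1 session (44/45 = 98% adherent), which few would call adherence, so the rows restricted to middling cut-offs are the fairer guide.

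**The case against.** The strongest reply is that little depends on these thresholds. The raw measures are named in advance, so adherence can be reported and compared without any cut-off. Adherence is not among the listed secondary outcome measures in Clinical Outcomes. Data Analysis plans no ODI analysis by adherence, and the primary comparison is by intention to treat. The text also says only that levels will be settled when the trial is complete; it does not say they will be chosen with outcomes in view. All of this stands, and it limits the point to one secondary objective and to any later adherence-based analysis.

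The reply does not remove the point. Objective (iv) is a stated between-group comparison, and the article ties adherence in two arms to thresholds set after completion, with nothing to keep that choice apart from the data. For walking, naming four quantities without a combining rule leaves a further choice open.

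It is also fair to object that the illustration describes a comparison the trial does not contain. That is correct, and the percentages are offered only to show how a free choice of cut-off behaves.

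A reader might further infer that usual-physiotherapy visits rise when a patient does badly, so that a high count means the reverse of good adherence. The article gives the therapist discretion over treatment but says nothing on how visits relate to progress. Only the missing denominator is supported.

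**Conclusion.** The point holds in a limited form and should be corrected. The thresholds for the class and walking arms are explicitly postponed until after the trial. Usual physiotherapy has no threshold or denominator, and no statement separates the choice of threshold from the adherence or outcome data.

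The size cannot be derived from the documents. Under the assumed attendance models, a free choice among middling common cut-offs takes a 5% false-positive rate to roughly 11 to 14%. Wider sets of cut-offs take it to between 19% and 24%.

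Two stronger readings are not supported. One is that the arms can be ranked in almost any order at will: this would need a threshold-only comparison in which every arm's cut-off is free, whereas usual physiotherapy has no cut-off and the raw measures are named beforehand. The other is that the ODI result, or every adherence-related explanation of it, is compromised: the primary analysis does not use the thresholds, and adherence could be examined on the raw measures. The documents show that steering is possible, not that it is intended.

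**What to change.** Replace the two sentences that postpone the thresholds with definitions fixed before any follow-up data are seen. Make the main adherence measure a continuous proportion in each arm:

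- **Exercise class:** classes attended out of 8.
- **Walking programme:** weekly walking targets met out of those set, with a stated rule for which diary quantities count as meeting a target.
- **Usual physiotherapy:** appointments attended out of those offered.

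If a cut-off is also wanted, the trial team should fix it in advance and label the resulting comparison descriptive. A common proportion does not make classes, walks and appointments equivalent. Walking targets are also individual and progressed each week from the previous week's diary, so that denominator moves with performance; the report should say so.

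The cost is small but goes beyond wording. Appointments offered must be added to the usual-physiotherapy treatment record forms, and each week's agreed walking target must be recorded, for example at the weekly telephone call. No treatment, visit schedule or sample size changes.
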